**Table 2 Tab2:** **Follow-up survey**

	**Baseline**	**Week 0**	**Week 2**	**Week 4**	**Week 12**	**Week 30**	**Week 52**
		**Session 1**	**Session 2**	**Session 3**	**Session 4**		
Inclusion		x					
Randomization		x					
Blankophor microscopy/Culture	X					x	X
/PCR							
Photo	X				x	x	X
Treatment		x	x	x	x		

### Data analysis

Estimating the proportion of patients with a complete cure rate to be 40% in the intervention group and 5% in the control group [27], with a power of 0.85, an alpha of 0.05 (2-tailed), the sample size should be at least 56. Accounting for loss to follow-up, the total sample size will be aimed at 64.

Data entry is done in duplicate by persons not otherwise involved in the study. All statistical analyses are carried out by a statistician blinded for treatment allocation. The Fisher’s Exact test will be used to test for differences between the treatment groups, and 95% confidence intervals (CIs) will be constructed for the differences in clinical and microbial cure rates. Normally distributed continuous variables will be compared using the Student *t*-test, and non-normally distributed variables will be compared with the Mann-Whitney *U* test. A significance level of less than 5% is regarded as significant. Analyses will be performed according to the intention-to-treat principle. Separate per-protocol analyses are planned in patients in whom all treatment sessions are performed and for analyses excluding re-infection. A sensitivity analysis is planned that regards completely cured patients at week 30 who have a new infection at week 52 as having a complete cure. All endpoints are evaluated at week 52.

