### Study endpoints

The primary endpoint is complete cure rate of the target nail. Complete cure is defined as a completely normal nail, or negative microbiological results in case minor abnormalities are present. A minor abnormality is defined as an irregularity of the nails with less than 5% of the surface area of the target nail at less than 1/4 of the distance of the distal nail edge without hyperkeratosis. Secondary endpoints are microbiologic cure rate of the target nail, complete clinical cure of all affected toes, complete clinical cure of the target nail, markedly clinically improvement of the target nail, onychomycosis severity index below 6 (in patients with scores >6 at study entry) of the target nail, changes in the affected surface of the target nail, changes in affected surface of all nails with a clinical diagnose of infection, free of subungual hyperkeratosis and changes in HRQOL. A ‘markedly clinical nail improvement’ is defined as a nail with less than 10% abnormalities and without hyperkeratosis after 52 weeks.

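### Fisher's exact test is a valid but conservative choice for the primary endpoint; an unconditional exact test with the same error control would gain about 2.5 power points at 64 patients in equal arms

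*Protocol article*

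**What the plan says.** The Study endpoints section makes the primary outcome binary: "The primary endpoint is complete cure rate of the target nail". The Data analysis section assumes a "complete cure rate to be 40% in the intervention group and 5% in the control group" and states that, "with a power of 0.85, an alpha of 0.05 (2-tailed), the sample size should be at least 56". It then adds a margin: "Accounting for loss to follow-up, the total sample size will be aimed at 64".

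For the comparison itself, Fisher's "Exact test will be used to test for differences between the treatment groups". The same section plans 95% confidence intervals for differences in cure rates, a 5% significance level and analysis by intention to treat. The Treatment assignment section describes randomization in blocks to two arms but gives no allocation ratio. The Trial status section says the trial is recruiting.

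**The concern.** Fisher's test conditions on the total number of cures. Randomization fixes the arm sizes but not that total, so the design does not require the conditioning. In small arms with a low control rate, the conditional distribution has few attainable values. The test then rejects under the null much less often than the nominal 5%, and the unused error rate is lost as power.

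The loss falls on the single primary comparison and is largest if laser cures fewer than the assumed 40%. One cure can decide the result: with 28 per arm, 5 laser cures against 0 sham cures gives a Fisher p-value of 0.051. The Discussion section says a finding of non-efficacy would be at least as relevant as a positive one, so an avoidable false negative would have consequences.

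**Working it through.** **Inputs.** Cure rates of 40% and 5%, two-sided alpha 0.05, power 0.85, required total 56 and target total 64, all from the Data analysis section. Allocation of 1:1 is an assumption; it gives 56/2 = 28 and 64/2 = 32 per arm.

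**Formulas.** Let x of n1 laser patients and y of n2 sham patients be cured.
- Fisher p-value, p_F(x, y): the sum of hypergeometric probabilities, given x + y, over all tables no more probable than the observed one. Fisher's test rejects when p_F ≤ 0.05.
- Probability of rejection at true rates (p1, p2): the sum of Bin(x; n1, p1) × Bin(y; n2, p2) over all rejected tables. This is power when p1 ≠ p2.
- Size: the maximum of that sum over p1 = p2 = p, taken on a grid of 1999 values of p from 0.0005 to 0.9995.
- Boschloo's test: reject when p_F ≤ c, where c is the largest cut-off that keeps the size at or below 0.05. Because c is at least 0.05, every table that Fisher's test rejects is also rejected here.

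**Step 1: the plan's own figure.** Fisher power at 40% against 5% is 0.840 with 27 per arm and 0.860 with 28 per arm. So 28 per arm, 56 in total, is the smallest equal-arm size reaching 0.85, and the stated 56 is reproduced. Other common formulas do not give it: the pooled normal formula gives 48, the same with continuity correction 60, and the unpooled and arcsine formulas 44 each.

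**Step 2: size and power with equal arms.** The Boschloo cut-off c is 0.0797 at 28/28 and 0.0746 at 32/32.

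| | 28/28 Fisher | 28/28 Boschloo | 32/32 Fisher | 32/32 Boschloo |
|---|---|---|---|---|
| Maximum size | 2.8% | 4.6% | 3.3% | 4.7% |
| Power, 40% vs 5% | 0.860 | 0.918 | 0.919 | 0.944 |
| Power, 35% vs 5% | 0.742 | 0.834 | 0.827 | 0.871 |
| Power, 30% vs 5% | 0.577 | 0.702 | 0.680 | 0.746 |

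At 32/32 the gains are 2.5, 4.4 and 6.6 points. At 28/28 they are 5.8, 9.2 and 12.5 points. With one sham cure, Fisher's test needs 8 laser cures and Boschloo's 7, at either size.

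**Step 3: slightly unequal arms (laser/sham), 40% vs 5%.**

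| Arms | Fisher size | Fisher power | Boschloo power | Gain (points) |
|---|---|---|---|---|
| 27/29 | 3.6% | 0.905 | 0.920 | 1.5 |
| 29/27 | 3.6% | 0.889 | 0.916 | 2.7 |
| 26/30 | 3.7% | 0.900 | 0.907 | 0.7 |
| 31/33 | 4.1% | 0.942 | 0.955 | 1.4 |
| 30/34 | 4.2% | 0.929 | 0.950 | 2.1 |

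The gain at lower rates depends on the split. At 30% against 5% it is 0.709 to 0.727 for 27/29, but 0.625 to 0.700 for 29/27.

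**Step 4: the version of the test matters.** SciPy's two-sided Boschloo test doubles the smaller one-sided p-value instead of ordering tables by the two-sided Fisher p-value. With unequal arms it can fail to reject where Fisher's test does:
- 4/31 vs 0/33: Fisher 0.0495, doubled version 0.062.
- 4/30 vs 0/34: 0.043 and 0.054.
- 4/27 vs 0/29: 0.048 and 0.052.

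**The case against.** The strongest reply is that nothing here is wrong. Fisher's test is conventional, valid and pre-specified, and the 56 already pays for its conservatism. A reader might infer from the unused alpha that the trial is underpowered or that test and sample size disagree. Step 1 shows the opposite, and this part of the objection stands in full.

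A reader might also take 2.8% as the error rate at the planned size. It belongs to exactly 28 per arm. The target is 64, where the figure is 3.3% with equal arms and about 4% with slightly unequal ones. Part of the large gain at 28/28 comes from exact balance, and losses to follow-up make equal analysed arms uncertain. This too stands. It shrinks the gain, but no configuration that was run gave a loss.

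It is tempting to add that Boschloo's test is never less powerful and costs nothing. The first holds only when the two-sided Fisher p-value orders the tables; step 4 gives counterexamples for the doubled version. The second overlooks the planned confidence interval, which should agree with the test, and the need to amend the wording during recruitment.

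Nor does Boschloo's test remove the conservatism at very low rates. With 28 per arm and 5% cure in both, it rejects about 0.6% of the time, against 0.1% for Fisher's test.

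**Conclusion.** The point holds as an efficiency improvement. The protocol names a valid primary test for which an exact alternative exists that keeps the error rate within 5%, rejects whenever Fisher's test does, and needs no extra patients.

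At the planned 64 in equal arms, the gain is 2.5 points at the design rates and 6.6 points if laser cures 30%. At 56 in equal arms, the corresponding gains are 5.8 and 12.5 points. With slightly unequal arms, about 1 to 3 points at the design rates is realistic.

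These figures rest on 1:1 allocation, which the article does not state, on 5% sham cure, and on ordering by the two-sided Fisher p-value. The documents do not support calling the planned test an error or the sample size inadequate: at the stated rates Fisher's test has 0.860 power with 56 patients and 0.919 with 64.

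**What to change.** Before unblinding, amend the analysis wording in three respects:
- Name Boschloo's unconditional exact test as the single primary test, with the two-sided Fisher p-value as ordering statistic. Rule out the doubled one-sided version explicitly, and check that the software computes the intended one.
- Take the planned 95% confidence interval for the difference in cure rates from a compatible unconditional exact method, so that test and interval do not conflict.
- Report Fisher's p-value only as a sensitivity result, so that two p-values on either side of 0.05 do not leave the primary conclusion open.

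The cost is a small amendment and a less familiar test to explain. The sample size and trial conduct do not change.

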## Methods/Design

Primary and secondary care patients with type 1 and type 2 diabetes mellitus with risk factors for developing diabetic foot ulcers and a clinical suspicion of onychomycosis will be recruited from a single-center podiatry practice. Patients will be included after written informed consent and microbiologic confirmation of onychomycosis.

Nail dust is collected from the target nail for microbiologic confirmation with blankophor microscopy, culture and polymerase chain reaction (PCR). PCR is regarded as the gold standard. The PCR is a real-time multiplex PCR based on amplification of ribosomal internal transcribed spacer regions and identification by probes specific for *Trichophyton mentagrophytes* species complex, *Trichophyton tonsurans*, *Trichophyton violaceum*, *Trichophyton rubrum* species complex, *Microsporum canis*, *Microsporum audouinii* and *Epidermophyton floccosum* as described by Arabatzis *et al.* [30].

The target nail is the nail with the highest onychomycosis severity index. The severity of onychomycosis is evaluated with the onychomycosis severity index (OSI) and standardized photographs are made [31]. Evaluation of treatment results will be done by an independent expert panel blinded for treatment allocation. The three experts are experienced health care providers who have experience in the treatment of patients with diabetic foot problems. Health-related quality of life (HRQOl) is evaluated at baseline and after follow-up with a generic questionnaire, the WHO-5, and a disease specific questionnaire the NailQOl [23]. The trial has received research ethics board approval from METC Isala Zwolle (NL46084.075.13/METC nr 13.0885).

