### Treatment assignment

Patients will be randomized in blocks using sealed nontransparent envelopes to either laser or sham treatment. A cloth between the head and his or her feet and a blinded goggle (which also protects the eyes) is used for blinding the subjects. The periprocedural sounds and lights during the laser application and the sham procedure are identical. The investigators are blinded for treatment allocation through the use of an independent second podiatrist who performs the interventions. An independent three-person panel blinded for treatment allocation evaluates the study outcomes using standardized photographs made at baseline, week 30 and at the end of follow-up. When consensus cannot be reached, decisions are made through majority voting.

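### Continuous secondary endpoints have a measured baseline but are compared with unadjusted tests chosen by normality; adjusting for baseline would gain precision at almost no cost

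*Protocol article*

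**What the plan says.** Under Study endpoints, the secondary endpoints include "changes in the affected surface of the target nail, changes in affected surface of all nails with a clinical diagnose of infection", as well as changes in health-related quality of life. Methods/Design says that quality of life "is evaluated at baseline and after follow-up with a generic questionnaire" (the WHO-5) and with the disease-specific NailQOL. Clinical follow-up has all nails assessed at baseline, week 30 and week 52, and Table 2 schedules photographs at these same times. A baseline value is therefore planned for each of these endpoints.

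Data analysis gives a single rule for continuous variables: "Normally distributed continuous variables will be compared using the Student" t-test, and those not normally distributed by the Mann-Whitney test. It names no covariate or regression model. It plans 95% confidence intervals only for differences in cure rates. It fixes week 52 as the time of evaluation, but does not say whether the tests use the change or the week-52 value.

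**The concern.** The method is stated, so this is more than a detail left for a later document. On one reading the tests compare change scores, which subtract the whole baseline value however weakly it predicts week 52. On the other they compare week-52 values and ignore baseline. ANCOVA estimates from the data how much of the baseline to remove, so in large samples it is at least as precise as either.

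Choosing the test by normality also leaves open, until the data are seen, whether the result is a difference in means or a comparison of ranks.

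At stake is how sharply the trial can describe its continuous secondary outcomes. The Discussion says that a finding of no efficacy would matter as much as a positive one, and such a finding is persuasive only with effect estimates and reasonably narrow intervals.

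**Working it through.** **1. The plan's own figure.** Data analysis assumes complete cure of 40% versus 5%, power 0.85 and two-sided alpha 0.05, and concludes that "the sample size should be at least 56". With 1:1 allocation (assumed; the ratio is not stated), the exact power of the planned Fisher test is 0.840 at 27 per arm and 0.860 at 28 per arm. So 28 × 2 = 56 is reproduced. The step to 64 implies a loss of 1 − 56/64 = 12.5%. Both figures concern the binary primary endpoint, and nothing below touches them.

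**2. Inputs for the continuous endpoints.** The article gives no SDs and no correlation. Write s0 and s1 for the SDs at baseline and week 52, and rho for their within-arm correlation. Values of rho from 0.3 to 0.7 are assumed.

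**3. Variance per patient, up to a common factor.**
- t-test on week-52 values: s1²
- t-test on change: s0² + s1² − 2·rho·s0·s1
- ANCOVA: s1²(1 − rho²)

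The second minus the third is (s0 − rho·s1)². This is never negative, and it is zero when rho·s1 = s0, that is, when the regression slope on baseline is 1.

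**4. Equal SDs (s0 = s1, assumed).** ANCOVA/change = (1 − rho²)/[2(1 − rho)] = (1 + rho)/2. ANCOVA/week-52 = 1 − rho². Interval width scales with the square root of these ratios.

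| rho | ANCOVA/change | interval narrower by | ANCOVA/week-52 | interval narrower by |
|---|---|---|---|---|
| 0.3 | 0.65 | 19% | 0.91 | 5% |
| 0.5 | 0.75 | 13% | 0.75 | 13% |
| 0.7 | 0.85 | 8% | 0.51 | 29% |

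**5. Unequal SDs.** With s1 = 1.5·s0 and s0 = 1, the change variance is 3.25 − 3·rho and the ANCOVA variance is 2.25(1 − rho²).
- rho 0.3: 2.0475/2.35 = 0.87, a gain of about 13%
- rho 0.5: 1.6875/1.75 = 0.96, a gain of about 4%
- rho 0.7: 1.1475/1.15 = 0.998, a gain of about 0.2%

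With s1 = 2·s0 and rho = 0.5, both variances equal 3, so the gain is zero. The ratio against week-52 values, 1 − rho², does not depend on the SDs.

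**6. Validity and power by simulation.** Normal data with equal SDs were simulated at 28 per arm, 4,000 runs per setting, with Shapiro-Wilk choosing between the t-test and Mann-Whitney. With no true effect, rejection rates were between 0.049 and 0.058 for the switched test on change, the switched test on week-52 values, and ANCOVA. With an assumed true difference of 0.6 SD, power was:

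| rho | switched test on change | switched test on week-52 | ANCOVA |
|---|---|---|---|
| 0.3 | 0.46 | 0.59 | 0.62 |
| 0.5 | 0.58 | 0.61 | 0.70 |
| 0.7 | 0.81 | 0.61 | 0.86 |

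**The case against.** The strongest case against is that nothing here is invalid. Only some secondary endpoints are involved, randomisation protects the t-test from bias, and baseline is not ignored if changes are analysed. That stands, and it limits the point to efficiency.

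The size of the gain also rests on quantities the article does not give. Equal SDs are doubtful for affected surface. Entry requires at least 25% involvement of the target nail, which truncates the baseline distribution, and the assumed 40% cure would put many laser-arm values near zero at week 52. Step 5 shows how far the gain over change scores can then fall. This also stands, so the size can be given only as a range.

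A reader might infer four stronger things that the documents do not support.
- **Inflated false positives from testing nails as independent records.** The article does not give the unit of analysis for the all-nails endpoint, and nowhere says that each nail is a record.
- **An equivalent number of patients lost, by dividing 56 by 0.75.** That 56 was set for the binary primary endpoint; no continuous endpoint was sized.
- **No treatment estimate from the Mann-Whitney branch.** A Hodges-Lehmann shift with an interval can accompany it on the measured scale; the article simply does not name one.
- **Change scores always over-correct.** They do so only when the slope on baseline is below 1.

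**Conclusion.** The point holds as a loss of precision in the continuous secondary endpoints. The planned tests are valid, and the primary Fisher analysis and the sample sizes of 56 and 64 stand.

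With equal SDs and rho between 0.3 and 0.7, baseline adjustment removes 35% to 15% of the variance of a change-score comparison, or 9% to 49% of the variance of a week-52 comparison. The first range falls towards zero as the slope on baseline approaches 1, for example when the week-52 SD is much larger than the baseline SD. The second depends on rho alone. That the method is unadjusted and switched by normality is read directly from the text; the size rests on assumed SDs and correlations.

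**What to change.** Replace the rule for continuous variables, as far as it governs the secondary endpoints, with wording such as: *Each continuous secondary endpoint will be analysed by ANCOVA of the week-52 value, one value per patient, on treatment arm and the baseline value of the same measure, with robust or bootstrap standard errors. The adjusted difference and its 95% confidence interval will be reported. A Mann-Whitney comparison will be a sensitivity analysis. No preliminary normality test will decide the method.*

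For the all-nails endpoint, state the per-patient summary, for instance the total or mean affected surface over the nails diagnosed as infected at baseline. Robust or bootstrap standard errors are advised because affected surface may be skewed, with many values at zero.

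The cost is a change of wording. The baseline and week-52 measurements are already scheduled, and no patients or visits are added. The article gives the trial status as recruiting, so the change can be made and dated before unblinding.

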## Discussion

Patients with diabetes who suffer from onychomycosis and neuropathy or PAD have an increased risk for developing diabetes-related foot complications, but also for treatment-related complications. New, effective and safe treatment modalities are needed for patients with diabetes who have risk factors for diabetes-related foot complications, in order to minimize the risks of developing ulcers and also to minimize discomfort and treatment-related complications caused by the current usual care.

The results of this study will provide the first double-blinded evidence for laser therapy and the first study in patients with diabetes mellitus with risk factors for developing diabetic foot ulcers. Positive results could aid in the prevention of diabetes-related foot complications since no local curative options are available, and systemic treatment could be avoided. If the results were to show safety and efficacy of laser therapy, this would provide the first high-level evidence for efficacy of a local treatment modality against onychomycosis. The results of this study will be at least equally relevant if they were to show non-efficacy since the use of lasers is becoming increasingly popular. In that case, unnecessary laser applications and possible harm could be avoided.

## Trial status

Recruiting.

## Abbreviations

CI: confidence intervals
FDA: Food and Drug Administration
HRQOL: health-related quality of life
OSI: Onychomycosis Severity Index
PAD: peripheral arterial disease
PCR: polymerase chain reaction
QoL: quality of life
